## Background

1

Spontaneous intracerebral hemorrhage (sICH) is the second most prevalent cause of stroke, and almost 1 million patients are diagnosed with sICH every year worldwide.^[1,2]^ sICH is associated with a high rate of mortality^[3]^ and disability.^[1,4]^

Recently, the management of blood pressure (BP) has been bone of contention for the sICH patients. Almost 90%^[5,6]^ of acute sICH patients have an elevated systolic BP (SBP) caused by the elevated intracranial pressure to keep cerebral blood +flow (CBF)^[7]^ and the highest SBP always appears at 24 hours after onset.^[8,9]^ The elevated BP increases the risk of hematoma expansion,^[10]^ while the acute lowering of BP may result in the ischemia of brain tissue.^[11]^

Several high-quality, multicentric, randomized controlled trials^[12,13]^ suggested the intensive BP lowering was safety in sICH patients and the ADAPT trial showed the peri-hematoma rCBF did not decrease after intensive BP lowering.^[14]^ A meta-analysis^[15]^ including 1427 patients also suggested that intensive BP lowering was safe and might have a potency of reducing hematoma expansion and improving clinical outcome. However, all of the mentioned randomized controlled trials and related clinical studies have no subgroup to discuss sICH with cerebrovascular stenosis and the management of BP for sICH patient with cerebrovascular stenosis is still unknown.

Brain ischemia has a high incidence of 25%^[16,17]^ in patients with sICH. The hematoma is surrounded by an ischemic penumbra, which needs adequate CBF to maintain its viability.^[18]^ The intensive SBP lowering may aggravate ischemia in ischemic penumbra and results in 20% of sICH patients suffering from the brain ischemia or infarction.^[11]^

The cerebrovascular stenosis has a rate of 20% to 54%^[19]^ in sICH patients, including intracranial cerebrovascular stenosis and extracranial cerebrovascular stenosis.^[20]^ The rate of intracranial cerebrovascular stenosis (16%) was higher than extracranial cerebrovascular stenosis (6%) in Chinese.^[21]^ Many researches^[22–26]^ demonstrated that 18% to 24% of ischemic stroke was closely associated with the stenosis of main cerebral vessels. When cerebrovascular stenosis coexists with sICH, intensive SBP lowering could increase the risk of ischemia and infarction.^[20,27]^

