### Sample size

2.4

The initial assessment of sample size is based on taking peri-hematoma rCBF as the ischemic reign of brain tissue.^[14]^ For no study now available referring to the field, the pilot trial was conducted to assess the sample size.

The pilot data includes 12 patients (6/each group) and shows the rate of reduction of peri-hematoma rCBF are (0.4282 ± 0.14705) and (0.3555 ± 0.12592) in intensive/conservative BP-lowering group, compared with that of contralateral homologous reign. For the reduction of relative rCBF, ≥44%^[28]^ is regarded as a threshold of infarction, if the difference of 2 groups is more than 9% (9%+35.5%>44%); acute SBP lowering is considered to significantly increase the risk of infarction in these patients. So, each sample size of 36 in a group will be required to detect a significant difference of 5% (2-tailed) and a power of 90% (PASS software Version 11.0.4; NCSS). In view of 10% patients lost to follow-up, a total of 80 patients (40 in each group) will be included in this trial.

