### Secondary outcomes

2.8

The key secondary outcome is the clinical outcomes (death and disability) at 90-day. Disability is considered as modified Rankin score from 3 to 5 point. The other secondary outcomes include incidence of other vascular events, hospital stays, and health-related quality of life measured from the EQ-5D at 90 days.

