### Statistical analysis

2.9

The analysis of this study is based on the intention-to-treat principle. The continuous variable of primary outcome and second outcomes will be assessed by *t* test. The Chi-square test will be used to assess the categorical data of second outcomes. Log-rank test will be used to analyze the time-to-event type of outcomes. Subgroup analysis will be conducted by level of cerebrovascular stenosis and location of the cerebrovascular stenosis.

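### A t test on hospital stay counts an in-hospital death as a short stay, and 90-day EQ-5D needs a value for patients who have died

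*Protocol article*

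**What the plan says.** Section 2.8 names the main clinical endpoint: "The key secondary outcome is the clinical outcomes (death and disability) at 90-day". Its other secondary outcomes are vascular events, "hospital stays, and health-related quality of life measured from the EQ-5D at 90 days". Stay and EQ-5D are the only continuous measures in that list.

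Section 2.9 opens with "The analysis of this study is based on the intention-to-treat principle" and continues: "The continuous variable of primary outcome and second outcomes will be assessed by" a t test. It then gives the chi-square test for categorical secondary outcomes and adds: "Log-rank test will be used to analyze the time-to-event type of outcomes". It does not say which outcomes are time-to-event.

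No section of the article says how a patient who dies enters the comparison of stay or of EQ-5D.

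**The concern.** Deaths must be expected in this trial, and the article allows that they may differ between arms. The Background says "sICH is associated with a high rate of mortality". It goes on to suggest that conservative treatment may reduce ischemia or infarction, events that it links to mortality. Section 2.11 has a stopping rule that depends on one group having higher mortality.

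Death affects the two outcomes in different ways:

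- **Hospital stay.** A patient who dies in hospital has a short observed stay. A comparison of mean stay cannot tell this from early recovery, so excess deaths pull an arm's mean in the direction usually read as benefit.
- **EQ-5D at 90 days.** A patient who has died cannot answer. Unless death is given a value, that patient has no observation, and the comparison is restricted by an event that occurs after randomization and may depend on treatment.

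At stake is a report in which stay, and possibly quality of life, is at odds with the death-or-disability result for a reason unrelated to recovery.

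**Working it through.** The article gives no planned figure for stay, EQ-5D or mortality, so there is nothing to reproduce. Its only sample-size calculation concerns peri-hematoma rCBF and does not enter here. All inputs below are assumptions, shown as ranges.

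**Hospital stay.** Let p be in-hospital mortality in an arm, S the mean stay of those discharged alive and D the mean stay of those who die in hospital. The arm's mean stay is (1 − p)S + pD. If S and D are the same in both arms and only p differs, the arm with more deaths has a mean stay shorter by

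shortening = Δp × (S − D).

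Assumed: S = 10 to 20 days, D = 3 to 5 days, Δp = 0.05 to 0.15.

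- Smallest: 0.05 × (10 − 5) = 0.25 days
- Largest: 0.15 × (20 − 3) = 2.55 days

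**EQ-5D.** Let m be the mean index among survivors, equal in both arms, and let Δp now be the difference in mortality by day 90. A survivors-only t test then estimates a difference of 0. With death scored 0, each arm's mean is (1 − p)m, and the arm with more deaths is worse by

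hidden loss = Δp × m.

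Assumed: m = 0.5 to 0.7, Δp = 0.05 to 0.15.

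- Smallest: 0.05 × 0.5 = 0.025
- Largest: 0.15 × 0.7 = 0.105

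**Simulation as a cross-check.** 40 patients per arm, 3,000 runs per scenario, with the same underlying distributions in both arms and only mortality differing. Assumed: median stay about 16 days, mean time to death 6 days, mean EQ-5D 0.60. Frailer patients are assumed to die more often, stay longer and score lower. Differences are the first-named arm minus the second.

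| Mortality | Stay, days | Stay: t test p < 0.05 | EQ-5D, survivors only | EQ-5D, death = 0 |
|---|---|---|---|---|
| 10% vs 10% | −0.02 | 5% | 0.000 | 0.000 |
| 20% vs 10% | −1.8 | 18% | +0.024 | −0.044 |
| 30% vs 10% | −3.3 | 47% | +0.047 | −0.092 |
| 30% vs 20% | −1.6 | 15% | +0.022 | −0.051 |
| 40% vs 20% | −2.9 | 41% | +0.047 | −0.103 |

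With equal mortality there is no shift, and the test rejects at about its nominal 5%. In every unequal scenario the arm with more deaths shows a shorter mean stay. The simulated shifts in stay can exceed the simple formula because frailer patients, who would have stayed longest, are the ones who die. The positive survivors-only EQ-5D differences also come from that frailty assumption. Without it the formula gives 0, a masked loss.

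**The case against.** **The EQ-5D part is not a stated error.** Section 2.9 does not say that deaths are dropped. A t test works equally well with death scored 0, and the full protocol or an analysis plan not shown may set that value. This stands. A reader might infer that the article fixes a survivors-only analysis, or that the t test is the wrong test for EQ-5D; neither is supported. What remains is conditional: if no value is assigned, the comparison leaves out randomized patients, against the stated principle.

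**Stay is not named in the t-test sentence.** Stay could be meant for the log-rank test, as time to discharge. This is possible, since no time-to-event outcome is listed. It does not remove the difficulty. If death is treated as discharge, the same bias returns; if it is treated as ordinary censoring, the analysis assumes that patients who died could still have gone home. Death has to be handled as a competing event. Nor does the article say that a shorter stay is better, although that is the usual reading.

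**Mortality is not hidden.** Death is part of the key secondary outcome, section 2.2 plans to look at death and dependency separately, and the monitoring board reviews safety every half year. This stands and limits the consequence.

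**The size is assumed.** The high mortality in the Background refers to sICH in general. Section 2.3.2 excludes deep coma, larger hematomas with an indication for emergency surgery, and serious prior disease, so deaths may be few. Nothing in the article establishes a mortality difference of 5 to 15 points. This stands too: with equal mortality the bias vanishes.

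**Conclusion.** The point holds for hospital stay. The t test that section 2.9 assigns to continuous secondary outcomes, applied to all randomized patients, favours the arm with more in-hospital deaths whenever mortality differs. The shift is 0.25 to 2.55 days under the assumed ranges. Limiting the test to survivors would instead leave out randomized patients.

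For EQ-5D the point is narrower. The t test may stay, but a value for death has to be fixed. Without one, a loss of about 0.025 to 0.105 can go unseen, assuming equal survivor means of 0.5 to 0.7 and 5 to 15 points more deaths.

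A reader might go further and conclude that the arm with more deaths would look better on EQ-5D. That needs the added assumption that frailer patients die more often; on the simple arithmetic the loss is only masked. A reader might also conclude that the trial would conceal a mortality difference. It would not, because death is in the key secondary outcome. The matter concerns lesser secondary outcomes and should be put right, but it does not threaten the main conclusions.

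**What to change.** In section 2.9, or in the analysis plan before the database is locked:

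- **Hospital stay.** Compare arms by a rank-sum test over all randomized patients, giving in-hospital death the worst rank. Alternatively, analyse time to live discharge with death as a competing event. Report stay in survivors descriptively only.
- **EQ-5D at 90 days.** Score death as 0 on the index and include all randomized patients. The t test may be kept.
- **Log-rank test.** Name the outcomes it applies to, so that it is clear whether stay is one of them.

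Days alive and out of hospital to day 90 is an option only if readmission dates are collected, which the article does not mention; it would also be a new endpoint and not just a change of wording.

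The recommended changes need only discharge date, date of death and the planned 90-day EQ-5D, so the cost is wording. The downside is that the stay result is no longer a plain difference in mean days.

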#### Exclusion criteria

2.3.2

(1)Known definite contraindication to intensive BP-lowering treatment (e.g., severe cerebrovascular stenosis (>70%), severe aortic valve stenosis, severe renal failure);(2)Known definite indication to intensive BP-lowering treatment (e.g., very high SBP ≥220 mm Hg; hypertensive encephalopathy; aortic dissection);(3)The ICH is caused by secondary factors (e.g., intracranial aneurysm; arteriovenous malformation; tumor stroke; anticoagulant correlation hemorrhage).(4)Glass coma scale ≤5 or deep coma;(5)Disabled or with underlying diseases (e.g., known dementia, severe cardiovascular disease, kidney failure) before onset;(6)History of ischemic stroke within 30 days before onset of sICH;(7)Known indication of emergency surgery (volume of supratentorial hematoma ≥30 mL or volume of infratentorial hematoma ≥10 mL; within 48 hours from onset; Glass coma scale ≥5);(8)Contraindication to CT perfusion imaging (CTP) (e.g., contrast allergy, pregnancy, or creatinine ≥160 mmol/L).

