### Randomization

2.5

Patients are assigned to intensive BP-lowering group and conservative BP-lowering group by a minimization random allocation system (minimpy 0.3). They are stratified by level of stenosis and location of stenosis. All information of patients is collected and randomization is stratified by a special researcher within 1 hour after admission in department of emergency. Once the group is determined, the allocation is not allowed to change unless quit from the trial.

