#### Imaging procedures

2.7.3

A standard NCCT and CTA are conducted when admitted in emergency department, by a 64-slice CT scanner (SOMATOM Definition Flash; Siemens Healthcare Sector, Forchheim, Germany). The scanning parameters of NCCT are 120 kVp, 340 mA, and 5 mm slice thickness. The hematoma volume is calculated by the ABC/2 method.^[30]^ CTA is initiated after the infusion of 100-mL contrast material (80 kVp, 110 mA, 1 mm slice thickness, and pitch 1:1). 3D reconstructions of CTA are performed to assess the level of cerebrovascular stenosis. NCCT (120 kVp, 340 mA, and 5 mm slice thickness) and CTP are conducted 24 ± 3 hours after randomization in order to assess for additional HE and perihaematoma rCBF with different treatments. The CTP will be initialed after the infusion of 42 mL contrast material given over 12 seconds with CT images acquired every 1.5 seconds at most 50 seconds (70 kVp, 150 mA, 1 mm slice thickness).

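### Cheap improvement: adjust the 90-day death-or-disability comparison for baseline prognosis and the two minimisation factors, rather than test it by an unadjusted chi-square alone

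*Protocol article*

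**What the plan says.** **Outcome.** Section 2.8 of the protocol article: "The key secondary outcome is the clinical outcomes (death and disability) at 90-day". Disability is defined there too: "Disability is considered as modified Rankin score from 3 to 5 point". The outcome is therefore binary.

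**Test.** Section 2.9: "The Chi-square test will be used to assess the categorical data of second outcomes". No covariate is named. Level and location of stenosis appear in that section only as subgroup variables.

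**Allocation.** Section 2.5 uses minimisation on two factors: "They are stratified by level of stenosis and location of stenosis". No other balancing factor is listed.

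**What is known at entry.** Age is an inclusion criterion (2.3.1). The coma score decides eligibility (2.3.2): "Glass coma scale ≤5 or deep coma". The admission scan gives the volume (2.7.3): "The hematoma volume is calculated by the ABC/2 method". Section 2.3.2 also uses volume in exclusion 7. Section 2.5 says that patient information is collected before allocation.

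**The concern.** Two sets of variables that could sharpen the 90-day comparison go unused.

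- **The minimisation factors.** Balancing on a factor and then leaving it out of the test gives up part of the precision that the balancing was meant to buy. This needs no outside figure.
- **Age, coma score and hematoma volume.** These are neither balanced nor adjusted for. The protocol itself treats the last two as marks of severity in its exclusions.

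The trial is sized on peri-hematoma blood flow alone (2.4), so the 90-day comparison has only the power that 80 patients happen to give. It is nevertheless the main clinical result. If the arms differ by chance in prognosis, an unadjusted test cannot allow for that particular draw, and covariates chosen after unblinding would carry little weight.

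**Working it through.** **1. The plan's own figures.** The only sample size is for blood flow: 36 per group, and 36/0.9 = 40 after 10% loss. No event rate or power is given for the 90-day outcome, so there is no figure to reproduce. Event rates and AUCs below are assumptions.

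**2. Overall validity.** Under no effect, with 40 per arm and three covariates, the simulated chi-square rejected in 4.2%, 4.4% and 5.2% of trials (AUC 0.74, 0.79, 0.83; 2,500 trials each).

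**3. How often prognosis is unbalanced.** The standardised difference between arms of 40 has SD sqrt(2/40) = 0.2236.
- P(|d| > 0.30) = 2 × (1 − Φ(0.30/0.2236)) = 2 × (1 − Φ(1.342)) = 0.180.
- P(|d| > 0.45) = 2 × (1 − Φ(0.45/0.2236)) = 2 × (1 − Φ(2.012)) = 0.044.
- At least one of three independent covariates beyond 0.30: 1 − (1 − 0.180)³ = 0.448 (independence assumed).

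The last figure describes a milder event than the first two do for a combined index. If one of three equally weighted covariates is off by 0.30 SD and the others are balanced, the index moves by only 0.30/sqrt(3) = 0.17 SD.

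**4. Conditional type I error of the chi-square** (20,000 trials, AUC about 0.74 to 0.83):

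| Imbalance in combined index | Conditional type I error |
|---|---|
| 0.17 SD | 4.2-4.6% |
| 0.30 SD | 7-8% |
| 0.45 SD | 12-18% |

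**5. Power, chi-square v Firth-penalised logistic regression.** The upper block has 36 evaluable per arm and all five covariates. The lower block has 40 per arm and three covariates.

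| Per arm | AUC | 35% v 60% | Gain (points) | 35% v 55% | Gain (points) |
|---|---|---|---|---|---|
| 36 | 0.61 | 56.1 v 55.6 | −0.5 | 37.8 v 38.1 | 0.3 |
| 36 | 0.65 | 56.2 v 58.2 | 2.0 | 39.8 v 41.1 | 1.3 |
| 36 | 0.74 | 54.6 v 60.6 | 6.0 | 37.8 v 43.3 | 5.5 |
| 40 | 0.74 | 63.3 v 67.8 | 4.5 | 45.4 v 47.9 | 2.5 |
| 40 | 0.79 | 63.2 v 71.0 | 7.8 | 45.8 v 52.0 | 6.2 |
| 40 | 0.83 | 62.4 v 75.6 | 13.2 | 45.9 v 56.4 | 10.5 |

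A separate run at 35% v 60% (1,200 trials per setting) gave gains of 2, 7 and 10 points at AUC 0.74, 0.79 and 0.84. At 40% v 60% the gains were 0, 7 and 10 points. The low AUC rows matter because exclusions 4 and 7 narrow the range of coma score and volume, which weakens their prognostic value.

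**6. Why a penalised model.** At 35% v 60% with 36 per arm, 36 × (0.35 + 0.60) = 34 events are expected. The model has six terms if each minimisation factor takes one, so 34/6 = about 6 events per term. Plain maximum likelihood rejected up to 6.5% under no effect. The Firth version rejected 3.5-5.5% with three covariates and 4.3-4.9% with all five at 36 per arm.

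**The case against.** The strongest reply is that an unadjusted chi-square in a randomised trial is a valid test whose 5% already allows for chance imbalance. That stands. A reader might infer from sections 2.5 and 2.9 that a 90-day difference could not be told apart from a difference in severity at entry. The documents do not support that as a general statement. It becomes a worry only when a large imbalance in prognosis has occurred, and the harmful size is rare. Nor may the 45% chance of some imbalance be joined to the 12-18% error, because they describe different events.

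The gain also depends on prognostic strength that the documents do not give, and the exclusions point towards the lower end. That stands too, and the range above reaches down to nil. Even with adjustment, power at 35% v 55% is at most 56% in these settings.

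A further reply is that an article leaves supplementary adjusted analyses to an analysis plan that is not shown. This is fair for extra analyses, but section 2.9 does name the test for categorical secondary outcomes, and the suggestion concerns that stated choice. The article also has no full baseline list. That age and coma score are recorded for every patient is inferred from the eligibility criteria.

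One might go on to ask for more minimisation factors. That is a separate design choice, which this point does not need.

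**Conclusion.** This is a cheap improvement, not an error in the plan. The chi-square keeps its overall type I error, but it discards baseline information already needed for entry, including the factors used in allocation. The protection gained matters in a minority of trials: an index imbalance above 0.30 SD occurs in about 18% and above 0.45 SD in about 4%, with 40 per arm. The power gain runs from about nil through 2-6 points to 10-13 points as the AUC rises from 0.61-0.65 through 0.74 to 0.83. All of this rests on assumed event rates of 35% v 55-60%, assumed AUCs and independent covariates. The direction is secure, since adjustment cost no appreciable power in any setting tried. The size is not.

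**What to change.** In section 2.9, prespecify that 90-day death or disability is analysed by Firth-penalised logistic regression with treatment, age, admission coma score, log admission hematoma volume, and level and location of stenosis as used in the minimisation. Report the adjusted odds ratio and a standardised risk difference, each with a 95% CI. The risk difference keeps the result readable beside the raw proportions. Keep the chi-square as a supportive analysis.

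The cost is one sentence of analysis wording and no new measurements, provided that the three entry variables are kept in the database. The downsides are that the short covariate list and its coding must be fixed before unblinding, and that the gain may prove small.

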### Data collection and management

2.10

Every patient included will have a unique study number. Allocation data will be collected by the special researcher and CRF will be filled by neurosurgeons with the study number. The follow-up data will be collected separately by another 2 trained investigators for the outcomes assessment. All data will be double inputted into a database and checked by Quality Monitoring Board (QMB) and the principal investigator, then be locked and sent to the statisticians.

### Safety and data monitoring

2.11

Safety and data of this trial are monitored by the data and safety monitoring board (DSMB), which involves neurosurgeons, neurologists, radiologists, and biostatisticians. They meet each other and review the data including rate of adverse effects and dropout once half a year. Adverse effect is defined as any unexpected events of the included patients during the study. Severe adverse event is defined as death or a vegetative state. All of adverse effects are recorded in the CRF by times, events, and treatment measures. The DSMB will stop the trial and modify the protocol if one of the groups has a higher mortality or rate of adverse effects than the other with a significant difference of more than 3 SD.

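### As written, the safety definitions and the only stated stopping trigger leave out the anticipated non-fatal ischemic stroke, and the 3 SD limit is undefined and insensitive to moderate harm in 80 patients

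*Protocol article*

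**What the plan says.** Section 2.11 (Safety and data monitoring) of the protocol article contains four relevant statements.

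- Adverse effects: "Adverse effect is defined as any unexpected events of the included patients during the study".
- Severe events: "Severe adverse event is defined as death or a vegetative state".
- DSMB meetings: the members "review the data including rate of adverse effects and dropout once half a year".
- Stopping: the DSMB is to halt the trial and change the protocol if one arm shows "higher mortality or rate of adverse effects than the other with a significant difference of more than 3 SD". The article does not say what the SD is the SD of.

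The Background (section 1) names the harm in question: "When cerebrovascular stenosis coexists with sICH, intensive SBP lowering could increase the risk of ischemia and infarction". It also says that intensive lowering may worsen ischemia around the hematoma and "results in 20% of sICH patients suffering from the brain ischemia or infarction". Later in the same section, lower rates of ischemia or infarction are put forward as a possible advantage of the conservative arm.

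Section 2.7.4 lists ischemic stroke within 7 days and the volumes of hematoma and ischemic region among the other primary outcomes. Section 2.8 lists other vascular events as a secondary outcome.

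**The concern.** The trial tests a strategy that its own Background suspects of causing infarction. An event that the protocol anticipates is, in the ordinary sense of the word, not unexpected. Taken literally, the definition removes that event from the adverse-effect count. The severe category does not bring it back unless the patient dies or becomes vegetative. Since the trigger uses only mortality and the adverse-effect rate, an excess of disabling but non-fatal strokes in one arm would not set it off.

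The limit adds a second difficulty. Without a defined SD, two DSMB members could compute different boundaries from the same data. On the most sensible reading, the boundary is so strict for a trial of this size that silence from the rule says little about moderate harm. At stake is whether the one written safety rule responds to the harm that motivates the trial.

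**Working it through.** **Step 1: trace a non-fatal ischemic stroke through section 2.11.**

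| Question | Text that governs | Result, read literally |
|---|---|---|
| Is it anticipated? | Background: "When cerebrovascular stenosis coexists with sICH, intensive SBP lowering could increase the risk of ischemia and infarction" | Yes |
| Is it an adverse effect? | Only unexpected events count | No |
| Is it a severe adverse event? | "Severe adverse event is defined as death or a vegetative state" | No |
| Is it in the trigger? | "one of the groups has a higher mortality or rate of adverse effects than the other" | No, unless fatal |
| Is it collected? | Section 2.7.4, other primary outcomes | Yes |
| May the DSMB see it? | The reviewed data are described as including, not limited to, adverse effects and dropout | Yes |

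The gap is therefore in the definitions and the trigger, not in data collection.

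**Step 2: the limit.** The article gives no operating characteristics for the rule, so there is no stated figure to reproduce. Inputs:

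- 40 patients per arm at full enrolment (section 2.4), and 20 per arm as an assumed mid-trial look.
- 3 SD read as three standard errors of the difference in proportions (assumption).
- True event rates assumed, because the article gives none for mortality or for adverse effects by arm.

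For event proportions p1 and p2 with n per arm:

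z = (p1 − p2) / √[p̄(1 − p̄) × 2/n], with p̄ = (p1 + p2)/2; the limit is crossed when z > 3.

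For a normal statistic, |z| > 3 corresponds to a two-sided p of 0.0027.

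**Step 3: smallest imbalance that crosses.**

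- 2/20 against 11/20: difference 0.45, p̄ = 0.325, SE = √(0.325 × 0.675 × 0.1) = 0.148, z = 3.04. With 10/20, z = 2.76.
- 4/20 against 14/20: difference 0.50, p̄ = 0.45, SE = 0.157, z = 3.18. With 13/20, z = 2.88.
- 4/40 against 16/40: difference 0.30, p̄ = 0.25, SE = √(0.25 × 0.75 × 0.05) = 0.0968, z = 3.10. With 15/40, z = 2.89.
- 8/40 against 21/40: difference 0.325, p̄ = 0.3625, SE = 0.1075, z = 3.02. With 20/40, z = 2.81.

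**Step 4: chance of crossing at a single look.** The two binomial distributions were enumerated exactly, and the probabilities of all pairs with z > 3 against the higher-rate arm were summed.

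| Assumed true rates | 20 per arm | 40 per arm |
|---|---|---|
| 5% vs 10% | 0.02% | 0.24% |
| 10% vs 20% | 0.5% | 2.7% |
| 10% vs 30% | 4.6% | 21% |
| 10% vs 40% | 18% | 58% |
| 20% vs 40% | 4.4% | 15% |
| 20% vs 60% | 33% | 77% |
| 25% vs 50% | 7.7% | 24% |

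With the unpooled standard error, 20% vs 40% gives 8.3% and 18.3%, so the conclusion does not depend on that choice.

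**The case against.** Four objections deserve weight.

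1. *The harm is watched.* A reader might infer that monitoring is blind to ischemic stroke. The documents do not support that. Stroke within 7 days and lesion volumes are outcomes, NCCT and CT perfusion are scheduled about 24 hours after randomization (section 2.7.3), the DSMB's review is not limited to adverse effects, and fatal strokes count in mortality. Nothing says that the DSMB may stop for no other reason. This stands in full and confines the point to the definitions and the stated trigger.

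2. *Unexpected may be loose English for untoward.* That is plausible in an article with other language slips, and on that reading a new stroke would count. But whoever records events works from the definition as printed, so the wording needs correcting on either reading.

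3. *The limit is conventional.* A reader might take 3 SD as three SDs of a yes/no variable, which is 3√(0.1 × 0.9) = 0.90 at a 10% rate and 3√(0.13 × 0.87) = 1.01 at 13%, and infer that the limit cannot be met. That is the least plausible reading, since the phrase is "with a significant difference of more than 3 SD", which points to the SD of the difference. Three standard errors is a recognised strict interim boundary. The number 3 is not an error. The missing definition is.

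4. *Large harm would be caught.* A reader might infer that the limit can hardly ever be reached. It can: at 40 per arm it is crossed with probability 58% for 10% vs 40% and 77% for 20% vs 60%. Low sensitivity to smaller differences largely reflects a sample of 80. This stands, and it is why the limit should be described honestly and need not be replaced.

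**Conclusion.** The point holds in a limited form. As printed, section 2.11 leaves the non-fatal ischemic stroke that the Background anticipates outside both safety definitions and outside the one stated stopping trigger. That follows from the text and needs no assumption beyond reading the word unexpected at face value.

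The SD in the limit is undefined. If it means the standard error of the difference, the rule is strict. For a doubling of the event rate from 5%, 10% or 20%, one look crosses with probability below 5% at 20 per arm and at most about 15% at 40 per arm. Very large differences are likely to be detected only near full enrolment. These figures rest on assumed true rates, a single look, a mid-trial look at 20 per arm and the pooled standard error.

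**What to change.** In section 2.11, and in the DSMB charter if there is one:

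- Define an adverse event as any untoward medical event, expected or not, and a serious adverse event by the usual seriousness criteria.
- Report ischemic stroke within 7 days and hematoma expansion by arm at each DSMB meeting, and add ischemic stroke to the events that the stopping rule compares.
- State the limit as the difference between arms divided by its standard error, naming the formula. The value of 3 can stay.
- State that this limit is insensitive to moderate harm at this sample size, so that the DSMB's judgement is not confined to it.

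A lower numerical threshold that prompts review without stopping is optional and for the DSMB to choose.

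The cost is an amendment to the wording and more events to report at each meeting. Sample size, blood pressure targets and the analysis of the key primary outcome are unchanged.
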